## Abstract

**Background**: Despite significant advancements in diabetes care, many individuals with type 2 diabetes (T2D) do not receive optimal care and treatment. Digital interventions promoting behavioral changes have shown promising long-term results in supporting healthier lifestyles but are not implemented in most healthcare offerings, maybe due to lack of general practice support and collaboration. This study evaluates the efficacy of the Digital, Individualized, and Collaborative Treatment of T2D in General Practice Based on Decision Aid (DICTA), a randomized controlled trial integrating a patient-centered smartphone application for lifestyle support in conjunction with a clinical decision support (CDS) tool to assist general practitioners (GPs) in optimizing antidiabetic treatment. **Methods**: The present randomized controlled trial aims to recruit 400 individuals with T2D from approximately 70 GP clinics (GPCs) in Denmark. The GPCs will be cluster-randomized in a 2:3 ratio to intervention or control groups. The intervention group will receive one year of individualized eHealth lifestyle coaching via a smartphone application, guided by patient-reported outcomes (PROs). Alongside this, the GPCs will have access to the CDS tool to optimize pharmacological decision-making through electronic health records. The control group will receive usual care for one year, followed by the same intervention in the second year. **Results**: The primary outcome is the one-year change in estimated ten-year cardiovascular risk, assessed by SCORE2-Diabetes calculated from age, smoking status, systolic blood pressure, total and high-density lipoprotein cholesterol, age at diabetes diagnosis, HbA1c, and eGFR. **Conclusions**: If effective, DICTA could offer a scalable, digital-first approach for improving T2D management in primary care by combining patient-centered lifestyle coaching with real-time pharmacological clinical decision support.

## 1. Introduction

Type 2 diabetes (T2D), a major contributor to the global burden of non-communicable diseases, is responsible for nearly one million deaths annually [1,2,3,4]. It significantly increases the risk of cardiovascular disease and other serious complications [5,6,7]. Approximately 300,000 adults live with diabetes in Denmark, of whom 90% are diagnosed with T2D [8]. The majority of these individuals also experience comorbidities such as hypertension, dyslipidemia, and obesity, which affect over 80% of patients [9]. Despite significant advances in clinical care, many individuals struggle to achieve recommended treatment targets, adhere to lifestyle changes, or receive optimal pharmacological treatment [10,11]. These persistent challenges underscore the need for strategies to support patient engagement and self-management.

Lifestyle interventions, particularly those focused on weight reduction, have consistently shown the potential to improve glycemic control and even achieve remission in a significant portion of patients with T2D [1,2,3]. Although traditional face-to-face interventions can be effective [12,13,14], barriers such as transportation, time constraints, and personal preferences often hinder participation [15]. In contrast, digital health solutions, including eHealth (web-based) and mHealth (mobile applications) technologies, offer scalable, private, and personalized support with real-time feedback [16,17,18,19]. Evidence suggests that these technologies can promote behavior change and improve health outcomes, particularly when integrated into routine care and supported by professional guidance [20,21,22,23]. Despite the evidence, digital solutions are not implemented in most healthcare offerings, which may be due to lack of support and collaboration [20].

The Digital, Individualized, and Collaborative Treatment of Type 2 Diabetes in General Practice Based on Decision Aid (DICTA) study is a randomized controlled trial designed to evaluate the clinical impact of a comprehensive, novel, fully integrated dual digital intervention for newly diagnosed T2D patients in Danish primary care. This approach combines two synergistic components: a personalized eHealth lifestyle coaching application that supports behavioral changes based on patient-reported outcomes (PROs) [17,20,21,22,23], and a clinical decision support (CDS) system integrated within electronic health records to guide evidence-based pharmacological decisions. Drawing on prior research and stakeholder input, DICTA emphasizes patient involvement, real-time data sharing, and tailored care strategies for caregivers that, in combination, might drive the way to a long-term sustainable improvement not only in body weight but for cardiac risk factors as well [17,20,23,24]. To our knowledge, this has not been performed before. The study aims to determine whether this integrated digital approach can enhance patient engagement, support sustained behavior change, and improve health outcomes compared to usual care.

## 2. Materials and Methods

### 2.1. Study Design

The DICTA study is a two-arm, cluster-randomized controlled trial (RCT) and will be conducted across multiple general practitioner clinics (GPCs) in Denmark. A randomization list will be generated using the program “sealedenvelope”, and cluster-randomization will occur at the GPC level, with an allocation ratio of 2:3 (intervention: control) and variable block sizes of 5 and 10 to ensure the balance between the two groups. Our allocation ratio of 2:3 is chosen based on an expectation that recruiting patients into the control group will be more challenging due to lower engagement incentives. Stratification will be based on two factors to ensure equal quality of care and no change in information sharing between study groups. Firstly, the GPC’s participation in the “Specialist supervised individualised multifactorial treatment of new clinically diagnosed type 2 diabetes in general practice (IDA): a prospective controlled multicentre open-label intervention study” [25] will be taken into consideration. Secondly, the physical address of the GPC will be considered. This is because some GPCs share address and health staff, and other GPCs operate as solo practices and thereby reduce the risk of intervention-based guidance of the control group patients. Other aspects such as age and gender of GPs, have not been taken into account as differences in quality of care is small and it is not possible to stratify on this. In Figure 1, the overview of the study’s elements is illustrated for both the intervention and control groups.

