### 2.2. Population and Recruitment

A total of 400 individuals will be recruited through approximately 70 GPCs. Only clinics using the XMO electronic patient journal (EPJ) from CompuGroup Medical Denmark A/S will be eligible. To participate, GPCs must agree to integrate both the CDS tool and the LIVA e-health lifestyle coaching application into their EPJ system for management of T2D.

Eligible patients will be identified through the Danish Centre for Strategic Research in Type 2 Diabetes (DD2). The DD2 and GPCs will jointly facilitate the distribution of written and oral information about the DD2 and the DICTA study. Patients expressing interest will be contacted via email and telephone by a study team member within one to two weeks to confirm eligibility.

The inclusion criteria of the DICTA study are as follows: age between 18 and 80 years, T2D for less than five years (since diagnosis) or no other glucose-lowering medication than Metformin, HbA1c ≥ 53 mmol/mole (changed to 48 mmol/mole and approved by Ethics Committee at 13 July 2023), participation in DD2 and DICTA by the patient’s GPCs, possession of a smartphone, and no previous use of digital coaching via LIVA. The following criteria will be used to exclude patients from the study: participation in other clinical health-related trials, presence of serious or life-threatening disease, cognitive impairment, diseases such as dementia or diseases inhibiting communication, pregnancy, or active pursuance of the same, suspicion of eating disorder, or insufficient Danish language proficiency.

Recruitment commenced in May 2021 and is expected to continue until 400 patients have consented to participate and initiated their involvement in the study. Figure 2 illustrates the expected patient flow in the DICTA RCT study. To keep up the inclusion rate, we planned from the start to continuously encourage GPCs from DD2 to join the study and to encourage participating GPCs to include more patients. Despite that, the inclusion rate was not as high as expected partly because of difficulties in meeting the initial inclusion criteria of HbA1c ≥ 53 mmol/mole because many of the patients were started early on Metformin, reducing HbA1c below 53 mmol/mole before inclusion in the study. Therefore, we reduced the inclusion criteria from HbA1c ≥ 53 mmol/mole to ≥48 mmol/mole in July 2023, which increased the inclusion rate.

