### 4.2. Analysis

In general, categorical variables will be summarized as numbers (%), continuous variables as min–max, mean (standard deviation, SD), and median (interquartile range, IQR), by randomization group.

The primary analysis of the primary outcome will follow an intention-to-treat principle, but due to the definition of the primary outcome, only participants with relevant measurement available at both baseline and one year of follow-up. We will employ a logistic regression model with robust variance estimation, accounting for GP clustering. As a secondary analysis approach, we will model the count of risk factors at both baseline and at one year of follow-up in a population-averaged longitudinal regression model based on generalized estimation equations (GEE), where group differences are included as a time-by-group interaction term. This approach accounts for clustering and potential missing measurements at each time point and will not be restricted to complete observations.

The analysis of the secondary outcomes will follow these two approaches outlined above. To generate hypotheses, several exploratory post hoc analyses will be conducted. The level for statistical significance is set at 5%. We will use statistical software such as StataBE (version 18.5 or newer) or R (version 4.5.1 or newer) for analysis.

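### The stated primary model is logistic for a continuous change and names no term for baseline SCORE2-Diabetes or the randomisation strata, although the 2:3 rationale implies that patients join with the clinic's arm known

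*Protocol article*

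**What the plan says.** Section 2.1 randomises clinics, not patients, 2:3 to intervention or control. It gives the reason for the ratio: an expectation that "recruiting patients into the control group will be more challenging due to lower engagement incentives". It also says "Stratification will be based on two factors": whether the clinic took part in the IDA study, and the clinic's physical address.

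Section 2.2 states that "A total of 400 individuals will be recruited through approximately 70 GPCs". A clinic's participation in DICTA is an inclusion criterion for its patients. The trial planned from the start to "encourage participating GPCs to include more patients". Patients are identified through DD2, DD2 and the clinics share the task of giving information, and a study team member confirms eligibility. Table 1 has the GP giving oral and written information in both arms. The HbA1c entry threshold was lowered from 53 to 48 mmol/mol in July 2023.

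Section 3 defines the primary outcome as the change in SCORE2-Diabetes over one year. HbA1c is one of its inputs.

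Section 4.2 restricts the primary analysis to participants measured at both times and states: "We will employ a logistic regression model with robust variance estimation, accounting for GP clustering". No covariate is named. The secondary approach is a GEE for a count of risk factors at baseline and one year, with a time-by-group interaction.

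**The concern.** Randomising clinics balances the clinics and the patients they serve. It does not balance the patients who agree to join once the clinic's arm is known. The protocol expects the incentive to join to differ by arm. Unequal allocation deals with how many join, not with who joins. The lowered HbA1c threshold adds a possible route to imbalance: if control recruitment runs later, the two arms could hold different mixes of patients who entered under each threshold.

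The stated model does not suit this setting. A logistic regression needs a binary outcome, and none is defined for the change in SCORE2-Diabetes. As written, the comparison of change takes no account of where patients started beyond subtracting it, and takes no account of the stratified randomisation. At stake are precision that could be had at almost no cost, and exposure to measured baseline differences.

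**Working it through.** **Is the arm known at recruitment?** The documents never say so outright. The steps are:
- The incentive to join can be lower in the control group only if the patient or the recruiter knows the arm when the patient is approached.
- Clinics must already be taking part before their patients qualify, and they keep adding patients.
- The GP informs patients in both arms, and no masking of recruiters is described.

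This is a strong inference, not a stated fact.

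**Does the secondary GEE condition on baseline?** With complete data and an identity link, the time-by-group term is (intervention at 12 months − intervention at baseline) − (control at 12 months − control at baseline). That is the difference in mean change. Baseline enters as an outcome and is not conditioned on. The GEE is also described for a count of risk factors, not for SCORE2-Diabetes.

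**Inputs for the arithmetic.** The documents give no correlation r between baseline and 12-month SCORE2-Diabetes, and no expected imbalance D. I assume r = 0.6 to 0.9, show the effect per 1 point of D, and take the variance s² to be equal at both times. The yardstick is the target difference in Section 4.1: 0.15 × 12.3 = 1.845, which the plan rounds to 2 points. The plan gives no figure of its own for baseline adjustment, so there is none to reproduce. The sample-size figure in Section 4.1 is not used here.

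**Precision, linear model.**
- Variance of the change: 2s²(1 − r).
- Variance of the 12-month score given baseline: s²(1 − r²).
- Ratio: (1 − r²) / [2(1 − r)] = (1 + r)/2.

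| r | variance ratio (1 + r)/2 | reduction |
|---|---|---|
| 0.6 | 0.80 | 20% |
| 0.7 | 0.85 | 15% |
| 0.8 | 0.90 | 10% |
| 0.9 | 0.95 | 5% |

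The standard error falls by the square root: √0.80 = 0.894 and √0.95 = 0.975, a reduction of about 11% to 2.5%. Clinic clustering is assumed to inflate both analyses alike.

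**Shift from a baseline imbalance, case 1: chance or regression to the mean.** An arm that starts D points higher is expected to fall (1 − r)D further without any treatment effect. For D = 1:
- r = 0.6: 0.4 points, which is 0.4/2 = 20% of the target.
- r = 0.9: 0.1 points, which is 0.1/2 = 5% of the target.

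If the intervention arm starts higher, the shift looks like benefit. If the control arm starts higher, it hides benefit.

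**Case 2: stable, systematic selection.** Suppose the arms come from populations whose risk differs by D at both times and treatment does nothing. The change-score difference is D − D = 0, which is unbiased. The baseline-adjusted difference is D − rD = (1 − r)D, so here adjustment brings in the error. The 0.1 to 0.4 points therefore belong to case 1 only.

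**The case against.** The strongest reply is that the article is silent, not contrary. Section 4.2 does not say that the analysis is unadjusted, and a covariate list commonly sits in a full protocol or SAP that is not shown. That stands: a reader might infer that adjustment is ruled out, and the text does not support this. Silence alone would not be a point. What the article does fix is a logistic model for a continuous change. That model has to be restated, and the restatement is the place to settle adjustment.

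Other objections also stand in part:
- A reader might infer that recruitment bias is established. It is not. The order of events is inferred, and DD2 and the study team share in recruitment.
- A reader might take 0.1 to 0.4 points as the expected bias. Case 2 in the working shows why it is not, and no imbalance figure appears in the documents.
- A reader might infer that adjustment cures the problem. The mechanism that the protocol names is incentive, and covariates do not remove selection on unmeasured motivation.
- A reader might infer that omitting the strata invalidates the intervals. They are usually too wide, so the loss is mainly efficiency.
- The variance ratio belongs to a linear model. In a logistic model, adjustment changes the odds ratio being estimated and does not generally shrink its standard error.
- The plan already has group summaries, a change-from-baseline outcome and a GEE. The summaries help to show imbalance, but neither the change score nor the GEE conditions on baseline.

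**Conclusion.** The point holds in a limited form, and the plan should be changed before the data are analysed. The protocol's own reason for 2:3 allocation makes measured baseline differences plausible. The stated primary model does not fit a continuous change and names neither the baseline score nor the stratification factors.

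The firmest gain is precision: variance at 0.80 to 0.95 of the change-score analysis, under a linear model and an assumed r of 0.6 to 0.9. The protection against imbalance is conditional. It is worth 0.1 to 0.4 points per point of imbalance if that imbalance is chance or regression to the mean, and the figure does not apply if selection is stable and systematic. Because the data may not show which case holds, both the adjusted and the unadjusted result should be reported.

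**What to change.** 1. State the primary model as a linear regression of 12-month SCORE2-Diabetes (or its change) on arm, adjusted for baseline SCORE2-Diabetes, IDA participation and the clinic-address factor as it was implemented, with robust variance clustered by clinic.
2. Optionally add a term for enrolment before or after the July 2023 HbA1c change.
3. Keep the unadjusted comparison of change as a sensitivity analysis.
4. Report the number recruited per clinic, and baseline characteristics, by arm.
5. State in the trial report that recruitment bias from unmeasured motivation cannot be excluded and is not removed by adjustment.

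The cost is analysis wording and routine reporting. The baseline score is already needed to form the outcome, so adjusting for it loses no participant from the primary analysis. The stratification factors are known from the randomisation. If further covariates are considered, check first that they are collected: sex, for example, is not listed in Table 2.

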### 2.2. Population and Recruitment

A total of 400 individuals will be recruited through approximately 70 GPCs. Only clinics using the XMO electronic patient journal (EPJ) from CompuGroup Medical Denmark A/S will be eligible. To participate, GPCs must agree to integrate both the CDS tool and the LIVA e-health lifestyle coaching application into their EPJ system for management of T2D.

Eligible patients will be identified through the Danish Centre for Strategic Research in Type 2 Diabetes (DD2). The DD2 and GPCs will jointly facilitate the distribution of written and oral information about the DD2 and the DICTA study. Patients expressing interest will be contacted via email and telephone by a study team member within one to two weeks to confirm eligibility.

The inclusion criteria of the DICTA study are as follows: age between 18 and 80 years, T2D for less than five years (since diagnosis) or no other glucose-lowering medication than Metformin, HbA1c ≥ 53 mmol/mole (changed to 48 mmol/mole and approved by Ethics Committee at 13 July 2023), participation in DD2 and DICTA by the patient’s GPCs, possession of a smartphone, and no previous use of digital coaching via LIVA. The following criteria will be used to exclude patients from the study: participation in other clinical health-related trials, presence of serious or life-threatening disease, cognitive impairment, diseases such as dementia or diseases inhibiting communication, pregnancy, or active pursuance of the same, suspicion of eating disorder, or insufficient Danish language proficiency.

Recruitment commenced in May 2021 and is expected to continue until 400 patients have consented to participate and initiated their involvement in the study. Figure 2 illustrates the expected patient flow in the DICTA RCT study. To keep up the inclusion rate, we planned from the start to continuously encourage GPCs from DD2 to join the study and to encourage participating GPCs to include more patients. Despite that, the inclusion rate was not as high as expected partly because of difficulties in meeting the initial inclusion criteria of HbA1c ≥ 53 mmol/mole because many of the patients were started early on Metformin, reducing HbA1c below 53 mmol/mole before inclusion in the study. Therefore, we reduced the inclusion criteria from HbA1c ≥ 53 mmol/mole to ≥48 mmol/mole in July 2023, which increased the inclusion rate.

### 2.3. Study Intervention

The DICTA intervention consists of two integrated components: a patient-directed eHealth lifestyle coaching program delivered via the LIVA application, and a clinician-directed CDS tool embedded into the EPJ system.
eHealth lifestyle coaching: Individuals with T2D in the intervention group will receive individualized digital coaching from a health coach through the LIVA application. PROs are shared with GPs and health staff via the EPJ, enabling tailored, data-driven lifestyle support.CDS: GPs receive real-time, individualized, algorithm-based pharmacological treatment recommendations for managing T2D, hypertension, and hypercholesterolemia, as appropriate.

The intervention is customized to each participant’s personal health goals, which will form the foundation for digital health coaching. GPCs will be supported by the CDS system in making evidence-based pharmacological decisions. Health professionals access real-time patient data on lifestyle and goals, facilitating individualized care. Figure 3 shows how all of the elements in this study are interconnected.

### 2.4. eHealth Lifestyle Coaching

During the intervention, participants receive personalized eHealth lifestyle coaching from a personal health coach via the LIVA app, developed by Liva Healthcare A/S. The health coach will be educated as a dietician and in addition, have completed a 20-h course in digital coaching. At baseline, participants in the intervention group will be provided with instructions for installing the application on their smartphone or tablet, along with a link to schedule their initial virtual meeting with their health coach. If the app is not installed and/or a meeting is not scheduled, Liva Healthcare will proactively contact the participant via email and/or telephone to offer assistance.

Within two to four weeks after the baseline examination, participants will be scheduled for a digital motivational interview with their assigned health coach. Throughout the intervention period, participants receive ongoing, personalized, relationship-driven, asynchronous coaching sessions from the same health coach, fostering a continuous and supportive relationship. These coaching sessions occur on a weekly basis for the first three months of the intervention period, subsequently transitioning to fortnightly intervals for the following nine months.

The content of these coaching sessions is multifaceted, delivered through text and video formats, and is tailored to the patients’ specific goals and preferences. They incorporate customized content and opportunities for peer-to-peer support [26]. The coaching sessions address participants’ manually and automatically recorded data from wearables, smartphones, and/or tablets. These include information on goal achievement, dietary habits, physical activity, and lifestyle plans. Additionally, the app delivers notifications and reminders to encourage regular data entry and sustained engagement. All patient interaction and guidance within the digital coaching platform are systematically logged and monitored throughout the study to assess adherence. This includes tracking session completions, frequency of patient engagement, and response to coaching prompts, ensuring adherence despite the asynchronous delivery format. Health coaches have access to PROs, including step counts, interval walking data [27], and other personalized goals, which are displayed on the health coach’s computer or tablet. Algorithms within the app monitor behavioral trends and alert the health coach to significant changes, such as decreased physical activity, prompting timely intervention.

The health coaches are trained to support participants in formulating SMART (specific, measurable, agreed upon, realistic, and time-based) goals and developing action and coping plans, including the identification of barriers and problem-solving strategies. For example, a SMART goal might involve reaching 6000 steps daily, tracked via the participant’s smartphone. A comprehensive description of the LIVA application is provided in Supplementary Material, Table S1.

